## Abstract

**Background:**

Despite the availability of guidelines for the specific treatment of hereditary angioedema (HAE) attacks, HAE morbidity and mortality rates remain substantial. HAE attacks are a major medical issue requiring specific treatment as well as a considerable socio-economic burden. We report a protocol designed to test whether a dedicated call centre is more effective than usual practice in the management of patients experiencing an HAE attack.

**Methods/design:**

This prospective, cluster-randomised, single-blind, parallel-group, multicentre trial evaluates the morbidity and consequent socio-economic costs of the management of patients experiencing an HAE attack by a dedicated call centre as compared to usual practice. The trial aims to recruit 200 patients. Patients in the intervention arm are provided with an SOS-HAE card with the call centre’s freephone number that they can access in the case of an attack. The centre’s mission is to provide recommended expert advice on early home treatment. The centre can route the call to a local emergency medical service with competency in HAE management or even arrange for the drugs needed for the specific treatment of an HAE attack to be sent to the emergency department of the local hospital. The primary outcome measure is the number of hospital admissions for an HAE attack. Each patient will be followed up every 2 months for 2 years. The study has been approved by the ethics committee (*Comité de Protection des Personnes d’Ile de France 10*; registration number: 2012-A00044-39; date of approval: 19 January 2012).

**Discussion:**

The SOS-HAE protocol has been designed to address the handling of attacks experienced by patients with HAE in the home. The proposed trial will determine whether the setting up of a dedicated call centre is more effective than usual practice in terms of reducing morbidity as given by the numbers of hospital admissions. The results are also anticipated to have important implications in terms of socio-economic costs for both healthcare services and patients.

**Trial registration:**

ClinicalTrials.gov NCT01679912.

## Background

Hereditary angioedema (HAE) is a rare disease. Worldwide prevalence ranges from 1/50,000 to 1/100,000 [1]. The form exhibiting C1 inhibitor (C1-INH) deficiency is an autosomal dominant disorder, although 25 % of cases are due to a spontaneous mutation in individuals with no family history of the disease [2, 3]. Patients with C1-INH deficiency may have type I or type II HAE [2, 3]. Patients with a family history of angioedema but with normal C1-INH levels may have a mutation of the gene encoding human coagulation factor XII (FXII-HAE) [2].

HAE attacks are characterised by recurrent subcutaneous swelling without itching lasting 48 to 72 hours [3, 4]. By far the most common sites of attacks are the extremities and abdomen, each accounting for nearly half of all attacks [5]. Abdominal attacks can cause severe pain and third-space fluid accumulation with resultant hypotension [5, 6]. Moreover, more than half of all HAE patients experience at least one laryngeal attack during their lifetime with the associated risk of asphyxiation [7]. Despite the availability of guidelines on specific treatments for HAE attacks, morbidity and mortality rates remain substantial [2, 3, 8].

The management of patients with HAE is shifting towards self-treatment of attacks at home with fewer visits to the hospital emergency department (ED) and fewer admissions [9, 10]. Even so, in a recent retrospective study of 193 HAE patients with 8 attacks/patient/year, approximately 11 % of patients visited the ED [11]. Moreover, according to a prospective observational study including 29 HAE patients, laryngeal and facial edemas are independent risk factors associated with hospital admission, and this is not avoided by early ED arrival [12]. A prospective study on the impact of measures, in particular specific home treatments, that might shorten the time from attack onset to first contact with a healthcare professional is required [12].

HAE attacks are not only an important medical issue but also a socio-economic issue [13]. Costs and hospital stays increase with attack severity [13]. A randomised study evaluating a telephone care-management strategy versus usual practice reported a significant decrease of average medical costs and hospital admissions in the telephone-coached group [14]. The aim of our multicentre, cluster-randomised, controlled trial is to determine whether a central dedicated call centre for HAE attacks that provides guidelines-based, standardised advice on early treatment would reduce the number of hospital admissions (morbidity) and thus the socio-economic impact of the disease.

## Methods/design

### Design and setting

The SOS-HAE trial is a prospective single-blind, two-arm, cluster-randomised, multicentre trial for patients with HAE attending a reference centre for bradykinin-mediated angioedema. Because the prevalence of HAE is low, the study will include only adult patients with an HAE diagnosis already confirmed by a specialist on the basis of patient history, functional and antigenic C1-INH levels and genetic data. Each investigator will select eligible patients (those with type I HAE, type II HAE or FXII-HAE) from amongst his/her reference centre’s customary patient population.

### Ethical aspects

The SOS-HAE study protocol and patient information sheets have been approved by the ethics committee and by the competent French authorities (*Comité de Protection des Personnes d’Ile de France 10; Hôpital Robert Ballanger*; registration number: 2012-A00044-39; date of approval: 19 January 2012).

Patients are informed orally and in writing (SOS-HAE information sheet) by the investigator and can refuse to participate. Written informed consent is required by French law, as the standard of care does not apply to both study arms.

### Participating centers

Eight French reference centres for bradykinin-mediated angioedema are participating in the trial. The centres were accredited in 2006 by the French Ministry of Health. Their mission is to improve access to diagnosis and therapy for patients with HAE. All eight centres have medical and paramedical teams with experience in the field of HAE, all implement a therapeutic education programme based on guidelines for systematic treatment of severe attacks and for prophylaxis of recurrent attacks, and all offer nurse-led sessions on self-administration of specific therapy for an attack [2, 3, 8, 15].

The freephone call centre ([name]) is hosted by the French emergency medical service (EMS) of a Paris suburb (SAMU 93) which has the logistics capabilities needed to provide 24/7/365 expert medical advice over the telephone [16]. SAMU 93 has promoted appropriate care of HAE attacks by (1) posting placards in SAMU 93 to enhance awareness and (2) providing their emergency physicians with instruction sheets on recommended emergency management of HAE attacks and prophylaxis of recurrence [2].

In France, each local EMS is equipped with one or more mobile intensive care units (MICUs), which include a senior emergency physician, a nurse and an ambulance driver. MICUs provide rescue techniques and medical advice, known as advanced life support, throughout France [16]. The local EMS facilities of each participating reference centre have the required logistics capabilities for storage and around-the-clock delivery of appropriate specific agents (plasma-derived C1-INH and icatibant) to patients or healthcare organisations [17]. If the case is life-threatening, SOS-HAE will immediately contact SAMU headquarters.

### Study population

Eligible patients are adults (≥18 years) with HAE at one of the eight participating reference centres. Inclusion criteria are a documented diagnosis of HAE (type I, II or FXII-HAE) and signed informed consent. Exclusion criteria are pregnancy, recent history (≤1 month) of myocardial infarction or ischemic stroke and allergy to icatibant or plasma-derived C1-INH.

Withdrawal of the study: withdrawal of consent follow-up.

### Randomisation

The randomised units are the reference centres (clusters) with randomisation stratified according to the number of eligible HAE patients by reference centre. Using permuted blocks of 4, we randomly assigned reference centres (not patients) to the intervention or to usual practice (1:1 ratio).

A modified version of Zelen’s method involving a two-step informed consent process was used for randomisation and inclusion [18]. Eligible patients were first invited to participate in a cohort study but without being informed of the nature of the study arms. Patients who agreed to participate in the study signed the first consent form. This was followed by verification of eligibility (compliance with inclusion/exclusion criteria) and centre randomisation. The patients in each centre were then offered inclusion in the arm assigned to their centre but without being informed of the nature of the other arm. Patients who agreed to be included signed the second consent form. The patient inclusion day is study day zero (D0).

### Study arms

The study protocol and randomisation arms are described in Fig. 1. The methodical management strategy of patients with HAE experiencing an HAE attack (SOS-HAE) was conceptualised after discussions of inclusion criteria and follow-up with a specialist in HAE. The protocol assesses the impact of the implementation of this strategy on number of hospital admissions in a group of patients rather than the actual efficacy of the treatment administered (Fig. 2)*.*

**Fig. 1 Fig1:**
[figure not shown]
Study design

**Fig. 2 Fig2:**
[figure not shown]
Study flowchart

### Intervention arm

All patients in the intervention arm are given an SOS-HAE card indicating what to do in the case of an attack: *“On attack onset and before taking any drugs, call the freephone number [name]*”. The physicians receiving the call at the call centre (open 24/7/365) have received special training as well as instruction sheets on emergency HAE management according to attack severity (Table 1). They can prescribe home treatment or route the call to a local EMS team with competency in HAE management. They can also make arrangements for specific drugs to be sent to the ED of the patient’s local hospital.

**Table 1 Tab1:** Treatment recommendations

Treatment	Recommendations
Vital distress	- Immediately and as soon as possible:
	- Administer icatibant (Firazyr®): 30 mg subcutaneously or
	- plasma-derived C1-INH (Bérinert®): 20 UI/kg intravenously
	- Switch the call to the local SAMU to send French EMS
	- Gain control of upper airway
Severe attacks	- Immediately and as soon as possible:
Laryngeal	- Administer icatibant (Firazyr®): 30 mg subcutaneously or
Facial	- plasma-derived C1-INH (Bérinert®): 20 UI/kg intravenously
Abdominal	- If treatments are unavailable at home, switch the call to the local SAMU to send an ambulance headed towards a hospital with specific treatments available or being able to get them by French EMS
	- Gain control of upper airway
Non-severe attacks (members, genitals)	- Tranexamic acid: 1 g/6 h except for patients who are breastfeeding or have thromboembolic pathology
Surveillance in all cases	Monitoring by phone 30 min, 1 h, 4 h, 12 h and 24 h after the beginning of the attack
	Advice to call back SOS-HAE call centre in case of secondary worsening

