## Discussion

Key priority issues in HAE management are reducing morbidity and mortality rates and socio-economic costs [2]. No study has ever been conducted to determine whether a central dedicated call centre for HAE attacks would reduce morbidity and the socio-economic impact of the disease.

The indications for the specific treatment of HAE attacks are well established. Plasma-derived C1INH and icatibant are the undisputed emergency drugs for life-threatening cases (laryngeal involvement), abdominal attacks and cases with facial involvement [2, 3, 20, 21]. Early home treatment is recommended [2, 15]. HAE patients trained in icatibant self-administration can recognise HAE attacks and decide when to inject [22], thereby avoiding hospital admission [12]. In an evaluation of the feasibility and efficacy of plasma-derived C1-INH in 31 patients with HAE, the time from attack onset to start of treatment was significantly shorter after than before training in self-injection [23]. Nevertheless, morbidity remains high in these patients. In one retrospective study, 73 patients (16 %) presented at the hospital ED with an attack and 59 % were admitted to hospital [13]. In another, 21 patients (11 %) presented at the hospital ED with an attack [11]. According to a recent prospective study, most of these patients visited the ED because they were short of medication or because they were unaware that emergency treatment could be self-administered. Our prospective controlled cluster-randomised trial would enable evaluation of the impact of a measure (dedicated call centre) that might shorten the time from attack onset to first contact with a healthcare professional.

HAE is a considerable economic burden both to the healthcare system and to HAE patients and their families [13]. Reducing the number of hospital admissions might help reduce this burden. We hypothesise that the use of a dedicated call centre providing expert advice for HAE might significantly reduce the number of admissions (morbidity rate) and thus the socio-economic costs associated with the disease.

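### Table 1 ties emergency dispatch for a laryngeal attack to home drug stock, yet asks for airway control in the same row and is not aligned with the protocol's rule for life-threatening cases

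*Protocol article*

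**What the plan says.** Four places in the protocol article bear on this point.

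- **Intervention arm, Table 1, severe attacks.** The row covers laryngeal, facial and abdominal attacks. It gives the specific drugs and then the routing line "If treatments are unavailable at home, switch the call to the local SAMU to send an ambulance". The stated destination is a hospital that holds these drugs or can obtain them through the EMS. The row closes with an instruction to secure the upper airway.
- **Intervention arm, Table 1, vital distress.** This separate row carries no condition on drug stock: "Switch the call to the local SAMU to send French EMS". It has the same airway line.
- **Participating centers.** "If the case is life-threatening, SOS-HAE will immediately contact SAMU headquarters". No attack site is named and home drugs are not mentioned.
- **Discussion.** In a sentence on drug indications, C1-INH and icatibant are called "the undisputed emergency drugs for life-threatening cases (laryngeal involvement), abdominal attacks and cases with facial involvement".

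The Background adds why the site matters: "more than half of all HAE patients experience at least one laryngeal attack during their lifetime with the associated risk of asphyxiation". For all attacks, Table 1 prescribes telephone monitoring at 30 min, 1 h, 4 h, 12 h and 24 h, and advice to call again on worsening.

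**The concern.** A laryngeal attack is the site that the protocol itself links to asphyxiation, so the instruction for that call should be readable in one way only. As printed, dispatch in the severe row depends on whether a drug is in the house, while another section makes contact with the SAMU (the French emergency medical service) unconditional for life-threatening cases. The only sentence that explains life-threatening attaches it to laryngeal involvement. The severe row also asks for something that needs a clinician at the bedside without saying who that would be when the drug is at home.

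Safety is the main stake. The second is the definition of the intervention: the Background describes it as standardised advice, and Table 1 is the only visible statement of that advice. EMS interventions are a secondary outcome, and dispatch rules feed that count directly.

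**Working it through.** The plan gives no figure on this point, and its sample size does not depend on it. The check is a comparison of passages.

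**Step 1. Which callers are affected?** Two readings of life-threatening in Participating centers are possible. The broad reading follows the Discussion and includes any laryngeal involvement. The narrow reading means only Table 1's vital-distress row.

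| Laryngeal attack | Table 1 | Participating centers, broad | Participating centers, narrow |
|---|---|---|---|
| With distress, drug at home or not | Call switched to SAMU | Immediate SAMU contact | Immediate SAMU contact |
| No distress, drug not at home | Call switched to SAMU | Immediate SAMU contact | Not addressed |
| No distress, drug at home | No switch instructed | Immediate SAMU contact | Not addressed |

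Only the last line can conflict, and only on the broad reading.

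**Step 2. Does the text choose between the readings?** No visible text defines life-threatening or vital distress, or equates them. The Discussion favours the broad reading: it pairs life-threatening with laryngeal involvement and lists abdominal and facial attacks separately, whereas Table 1 groups all three sites. The two-tier layout of Table 1 favours the narrow reading.

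**Step 3. Does the narrow reading clear everything?** No. In the vital-distress row, the airway line goes with the dispatch of a team that can act on it. In the severe row with the drug at home, the instructed follow-up is by telephone, so no one is designated to carry the line out. On the broad reading the cross-section conflict stands; on the narrow reading the airway line is still unexplained. Either way some text needs repair.

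**Step 4. How many calls?** The protocol's planning figures give 100 intervention patients × 8 attacks per year × 2 years = 1,600 attacks. The laryngeal share is not stated; the Background says only that extremities and abdomen each make up nearly half. Assuming 1% to 5%:

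- 1,600 × 0.01 = 16
- 1,600 × 0.05 = 80

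Within that assumed range these are upper counts, because only attacks without distress and with a drug at home are affected, and neither proportion is given. They describe possible exposure to the unclear rule, not admissions gained or lost.

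**The case against.** The strongest reply is that the plan describes an ordinary triage: acuity first, then site. On that view, life-threatening in Participating centers is simply the vital-distress row, and a laryngeal attack with distress already goes to the SAMU unconditionally. The Discussion sentence concerns which drugs to use, and there it agrees with Table 1. This reading is plausible, and nothing printed excludes it. A reader might infer that the protocol contains two incompatible routings for every laryngeal attack; the documents do not support that, because no passage states a second routing rule for laryngeal attacks by name.

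Escalation is also provided for. Monitoring and call-back apply in all cases, the physicians are trained, and the Intervention arm text lets them route a call to a local EMS team without tying this to drug stock. Table 1 does not forbid sending someone when the drug is at home. This softens the airway point but does not remove it: discretion to send help is not an instruction that says who carries out a listed step.

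One could also say that the extracted table is unreliable, since the conditional line happens to sit beside the abdominal label. But a line-by-site reading would split the two drug alternatives, which are joined by an or, between laryngeal and facial attacks. All the lines lie between the severe and non-severe labels, so treating them as one block is the sensible reading.

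Finally, the article condenses fuller instruction sheets, which are not shown and may be clear. That would excuse an omission, but it does not reconcile the printed statements.

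**Conclusion.** A limited patient-safety inconsistency stands. For a laryngeal attack without distress and with the drug at home, Table 1 instructs no dispatch yet lists airway control. It also conflicts with Participating centers unless life-threatening there is confined to vital distress, which the text does not say. The cross-section conflict therefore rests on reading two sections together; the airway problem rests on Table 1 alone.

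On trial results, the count of EMS interventions may be affected, because the rule governs dispatch. A reader might go further and infer that the primary outcome is compromised, particularly as the Background names laryngeal swelling among the predictors of admission. The documents do not support that. An admission is an inpatient stay of more than 12 hours, so dispatch is not admission, and the share of affected calls is not given. There is one call centre and one table, and nothing shows that its physicians would act on different sections. The effect on admissions cannot be quantified, and the 16 to 80 attacks rest on an assumed share. No sample size or analysis changes.

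**What to change.** The sponsor and its HAE specialists should reconcile Participating centers, Table 1 and the Discussion:

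- State whether life-threatening and vital distress are the same tier, and use one term throughout.
- State which Table 1 row a laryngeal attack without distress belongs to, and whether SAMU contact then depends on drugs at home.
- Make the airway-control line of the severe row consistent with who is present under that routing.
- Check the instruction sheets against the agreed wording and brief the call-centre physicians.
- Record the date of any change, so that EMS interventions before and after it can be told apart.

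Which clinical rule applies is for the sponsor and its specialists; none is proposed here. The cost is one revised table row and instruction sheet, matching wording in two other sections, and a briefing, with no extra patients or procedures. Recruitment ended in June 2014 and follow-up lasts 2 years, so the instructions could govern calls until about June 2016.

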#### Usual practice arm

No changes are made to usual practice treatment, and patients are not given the SOS-HAE card.

### Data collection and follow-up

#### Medical data

HAE specialists and emergency physicians collect standardised clinical data including those presented in the most recent Hereditary Angioedema International Working Group (HAWK) guidelines [2]:On day zero (D0): Patient sex, age, type of HAE (type I, II or FXII-HAE), time since diagnosis, personal history of angioedema (ED visits during previous year, admissions to intensive care unit (ICU) and history of intubation and tracheotomy), ongoing long-term treatment and number of relatives with HAEAt each attack and every 2 months for 2 years: Number of attacks and, for each attack: possible trigger of attack, day and time of onset of symptoms, day and time of call to SOS-HAE centre, edema site, home therapy (self-administered or caregiver) or hospital treatment, time treatment started and course of attack (onset of symptom relief and time of symptom resolution)Number of admissions/patient/year over 2 years, duration of admissions, number of admissions to ICU/patient/year over 2 years, number of ED visits/patient/year over 2 years, number of intubations, number of interventions by EMS and mortality

#### Health economics data

Call centre costs include freephone, training of EMS personnel and answering of calls (time spent and number of calls).

Patient care costs include consumption of hospital resources (admissions) and out-of-hospital resources (ED visits or emergency ambulance, drugs to treat attacks and their administration by physicians or nurses), working days lost and any remaining costs supported by patients.

#### Quality of life

The Short Form Health Survey (SF-36) score is measured after 1 year and after 2 years of follow-up.

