#### Secondary outcomes

Secondary outcomes are the number of admissions for a cause other than an angioedema attack per year over a 2-year period, mortality from an angioedema attack, mortality from another cause, number of ICU admissions per year, number of ED admissions per year, number of hospital stays, number of intubations per year, number of interventions by EMS, number of working days lost and their duration, costs of patient care and SF-36 score.

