#### Analysis of secondary outcomes

Secondary outcomes will be analysed using a mixed model ANOVA. The family will be introduced into the model as a random effect. All tests will be two-sided.

Number of admissions for a cause other than an angioedema attack per year for 2-year-period, mortality from an angioedema attack, mortality from another cause, number of ICU admissions per year, number of ED admissions per year, number of hospital stays, number of intubations per year, number of interventions by EMS, number of working days lost (and duration), costs (hospital and ambulatory costs) of patient care and SF-36 will all be estimated in each arm for 2 years.

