### Trial status

Recruitment for the trial was completed in June 2014.

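### SF-36 has no day-zero score and its stated model leaves out centre, the randomised unit: the first costs precision, the second understates the standard error

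*Protocol article*

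**What the plan says.** In the protocol article, the section Quality of life gives the whole SF-36 schedule: the score "is measured after 1 year and after 2 years of follow-up". The section Medical data itemises what is recorded at entry. The list opens with "On day zero (D0): Patient sex, age, type of HAE (type I, II or FXII-HAE), time since diagnosis" and goes on to "personal history of angioedema (ED visits during previous year, admissions to intensive care unit (ICU) and history of intubation and tracheotomy", then long-term treatment and the number of affected relatives. It contains no quality-of-life measure.

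SF-36 closes the list under Secondary outcomes: "costs of patient care and SF-36 score". Under Analysis of secondary outcomes the article states: "Secondary outcomes will be analysed using a mixed model ANOVA", and then: "The family will be introduced into the model as a random effect". No other random effect and no covariate is named.

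Under Participating centers and Randomisation, the randomised units are eight reference centres allocated 1:1. Patients sign the second consent and enter their arm after centre randomisation. Under Trial status: "Recruitment for the trial was completed in June 2014".

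**The concern.** Two features of the plan bear on how far an SF-36 difference can be trusted.

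First, there is no entry score. A baseline SF-36 would normally be the strongest predictor of the later score, so adjusting for it would narrow the interval. It would also show directly whether the patients who accepted their arm differed at entry. That matters here because the second consent follows centre allocation and the clinical staff are not blinded.

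Second, the stated model accounts for relatedness within families but not for the unit that was randomised. If SF-36 varies between centres for any reason other than the strategy, patients of one centre are not independent. A model without centre then counts about 100 patients per arm as if each had been allocated separately, when about four centres per arm were.

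SF-36 is the trial's only quality-of-life outcome. What is at stake is a claim of a quality-of-life benefit or harm that rests on too small a standard error. This point does not concern the primary outcome.

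**Working it through.** **Inputs from the article.** Sample size calculation: 100 patients per arm, design effect 1.4. Participating centers: eight centres. Randomisation: 1:1.

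**Assumptions.** Four centres per arm (from the 1:1 ratio), 200/8 = 25 patients per centre, and SF-36 in SD units. The article gives no intracluster correlation (ICC) for SF-36, so a range is shown.

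**The plan's own figure.** The article gives no figure for SF-36. Its 100 per arm for the primary outcome is reproduced with the unpooled formula for 88% against 68%, 85% power and two-sided 5%:

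(1.960 + 1.036)² × (0.88 × 0.12 + 0.68 × 0.32) / 0.20² = 72.5, and 72.5 × 1.4 = 101.6.

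The pooled formula gives 76 × 1.4 = 106.4. Nothing below depends on which was used. Only the 100 and the 1.4 are carried forward.

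**Step 1: implied ICC.** Design effect = 1 + (m − 1) × ICC, so ICC = 0.4/24 = 0.017.

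**Step 2: standard error of an arm difference.**
- Ignoring centre: √(2/100) = 0.141 SD.
- Allowing for centre: √(2 × 1.4/100) = 0.167 SD.
- Ratio: √1.4 = 1.18. The model without centre understates the error by about 15% (1 − 1/1.18).

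**Step 3: effect on the test.** With no true effect, a test that ignores centre rejects with probability 2 × [1 − Φ(1.96/√1.4)] = 2 × [1 − Φ(1.656)] = 0.098.

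**Step 4: simulation.** Eight centres of 25, no effect, 8,000 runs per row:

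| ICC | Design effect | True SE (SD) | Rejects, centre ignored | Rejects, t-test on centre means (6 df) |
|---|---|---|---|---|
| 0 | 1.0 | 0.141 | 5.2% | 5.0% |
| 0.017 | 1.4 | 0.167 | 9.7% | 4.9% |
| 0.05 | 2.2 | 0.210 | 18.6% | 5.3% |
| 0.10 | 3.4 | 0.261 | 29.3% | 4.8% |

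The second row agrees with step 3. The last column shows that the nominal level is recovered without any baseline score once the analysis respects centre.

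**Limit of the simulation.** It has no family structure. A family random effect could absorb part of the between-centre variation where several relatives take part, but it still treats families of the same centre as independent. The column that ignores centre is therefore a guide to the stated model, not an exact figure for it.

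**The case against.** The strongest reply is that centres are randomised. Chance differences at entry have expectation zero and form part of the sampling error of a follow-up-only comparison. An analysis with the right cluster variance counts them, and no baseline is needed for validity. This stands, and the last column of the table shows it. A reader might infer that, without a day-zero SF-36, a quality-of-life difference cannot be told apart from one present at entry. The documents do not support that reading. What randomisation does not cover is selection at the second consent. The article gives no evidence that such selection occurred, only that the order of events allows it.

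A reader might also calculate that, at a standard error of 0.167 SD, an entry difference of 0.2 SD or more arises in about 23% of allocations and one of 0.3 SD or more in about 7%. These are tail areas of the estimator's own error under a borrowed design effect. They are not probabilities of bias. Nor can the usual variance saving from adjusting for a baseline be claimed here. It would belong to a baseline SF-36 that was not scheduled, and says nothing about what the recorded day-zero items would gain.

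A second reply is that covariates for one secondary outcome belong in an analysis plan. This also stands. That the article names no covariate is not an error, and its text does not rule covariates out. Centre is different, because the article does state the random-effects structure and leaves out the randomised unit. An analysis plan could add centre or covariates, but could not supply an entry score that was never scheduled.

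**Conclusion.** The point holds in a limited form. The missing entry score costs precision and removes the direct check on post-allocation selection. It does not by itself invalidate the comparison. The model as stated would understate the SF-36 standard error if scores vary by centre: 0.141 SD in place of 0.167 SD at a design effect of 1.4, with about 10% rejections at a nominal 5%.

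This rests on equal centres of 25, four per arm, and a design effect set for the primary outcome and only assumed for SF-36. Over ICC 0 to 0.10 the false-positive rate runs from 5% to 29%, so there is no inflation if SF-36 does not vary by centre. The matter is minor in weight, being one secondary outcome, but the correction is nearly free.

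**What to change.** Before the analysis, replace the SF-36 part of the secondary analysis with one linear mixed model for the scores at 1 and 2 years that has:

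- strategy, time and their interaction as fixed effects, with repeated scores linked within patient;
- centre as a random effect, keeping family;
- a small-sample degrees-of-freedom correction suited to eight clusters;
- a short, prespecified set of day-zero covariates already collected, for example prior-year ED visits, HAE type, long-term treatment, age and sex.

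Report the result as a between-arm difference at each time, and state that no baseline SF-36 exists and that change from entry cannot be estimated. The article does not promise such a change, so this only guards the later report.

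Recruitment has closed, so a day-zero SF-36 cannot be added for this cohort. The covariates stand in for it only in part. How much precision they add is unknown, and they can reduce but not exclude a difference due to selection.

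The cost is analysis wording, with no new data. The interval becomes wider than the stated model would give. With 6 degrees of freedom the 95% half-width at a design effect of 1.4 is 2.447 × 0.167 = 0.41 SD, against 1.96 × 0.141 = 0.28 SD when centre is ignored, both before any gain from covariates.
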